### 11.3 Statistical criteria of termination of trial

NA

### 11.4 Planned Analyses

Detailed methodology for summaries and statistical analyses of the data collected in this trial will be documented in a statistical analysis plan. The statistical analysis plan will be finalised before database closure and will be under version control at the Clinical Trial Unit, University Hospital Basel. Deviations from the analyses described below will be listed in a separate section of the analysis plan.

#### 11.4.1 Datasets to be analysed, analysis populations

The full analysis set (FAS) consists of all patients who are randomised.

The intention-to-treat (ITT) set is a subset of the FAS that consists of all patients for whom the primary endpoint is available. Patients are assigned to the treatment arm they are randomised to.

The per protocol (PP) set includes the same patients as the ITT set, but patients are assigned to the treatment arm that corresponds to the actually obtained treatment.

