### 7.4 Criteria for withdrawal / discontinuation of participants

The decision about all pharmacological therapy, including unplanned glucocorticoid treatment, will entirely rest with the treating physician, not the study team. Unplanned (rescue) glucocorticoid treatment may also be initiated by the

---

participating patient in case of symptoms of glucocorticoid deficiency (see also section 8.6. below). The trial compares two regimens with an approved drug in registered indications, thus there are no withdrawal criteria concerning drug-related aspects. Rather, unplanned (rescue) glucocorticoid treatment will be assessed as component of the primary outcome.

Reasons for exclusion of a patient include withdrawal of informed consent or non-compliance. Study subjects may choose to withdraw from the trial, both during the treatment or follow-up phase, without justification. Substitute patients for drop-outs will be recruited. See also point 9.2.5 below.

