### **8.5 Data Collection and Follow-up for withdrawn participants**

Patients who choose to withdraw from the study during the treatment intervention will be considered as drop-outs. Patients who choose to withdraw from the study during the follow-up period (i.e. refuse to participate in the telephone interviews on days 35, 90, and 180 or to come to the outpatient visit on day 35, if applicable) will be asked for permission to contact their treating physician for inquiry of the 1° outcome and to use their data collected so far. This will prevent their drop-out. If patients do not permit the inquiry of the 1° outcome, their data will be considered right-censored from the last documented contact onward.

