### 9.2 Assessments of outcomes

#### 9.2.1 Assessment of primary outcome

Assessment tools of 1° outcome measures:

- Questionnaire: Hospitalization? Unplanned glucocorticoid therapy? Adrenal crisis?
- Treating physician interview: Death?

The 1° outcome can be assessed during a telephone interview with the patient using a questionnaire.

If a patient cannot be reached, the treating physician will be contacted to inquire about the possibility of the patient's death.

The 1° outcome will be assessed by telephone on days 7, 28, 35, 90, and 180; ± the variations indicated in the study flow chart. Additionally, a subgroup of 180 patients living near their respective trial site will be seen for a clinical visit on study days 7 and 35. These clinical visits include vital signs (heart rate, blood pressure in recumbent and upright positions), and a 250 mcg Synacthen® test.

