- The non-inferiority margin is defined as an absolute increase of the event rate by 13% over 6 months. We used a modified Delphi approach to determine this margin. 10 experienced clinicians board-certified in internal medicine and/or rheumatology, gastroenterology, and endocrinology were individually asked to define the maximum increase in outcome events they would accept for the benefit of rapid glucocorticoid stop and gain of high-quality scientific data in the area of steroid withdrawal. Assuming an event rate of 40% in the standard treatment arm, the mean tolerable increase under experimental treatment was 13.6% (range, 5 to 20%; median, 13%).
- The significance level is 5%.

For each combination of the noninferiority margins 7.5%, 7.6%, ..., 17.5%, and the sample sizes  $n = 200, 210, \dots, 1200, 999$  individual data sets were simulated based on the above assumptions. A Cox proportional hazards regression model was fitted to each data set, and the hazard ratios for the experimental vs. the control arm with the associated 95% confidence interval were estimated. Noninferiority was concluded if the upper limit of the two-sided 95% confidence interval of the hazard ratio was below the critical hazard ratio (see above equation). The power was estimated as the proportion of positive conclusions divided by the total number of the 999 iterations per parameter combination. To achieve a power of 80%, 573 patients (95% CI, 565 to 580) need to be included, assuming an event rate of 40% over the 6 months follow-up period and setting the non-inferiority margin to 13% (Figure). The critical hazard ratio for this noninferiority scenario is 1.478.

The sample size of  $n=573$  is a conservative estimation, since the assumed drop-out rate of 10% is relatively high.

[figure not shown]

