### **11.5 Handling of missing data and drop-outs**

We will strive to make a complete case analysis, which will likely be feasible because the primary outcome is composed of clearly defined clinical events that can easily be tracked and inquired from the treating physicians if necessary. If a substantial proportion of patients have missing data, we will consider the use of multiple imputation.

Patients who leave the trial during the blinded treatment phase are replaced only if the number of total drop-outs is >10%.

---

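### ITT and PP membership depends on the primary endpoint being available, and the outcome inquiry written for later withdrawers is not extended to patients who withdraw during the four treatment weeks

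*Protocol*

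**What the plan says.** **Analysis sets.** Section 11.4.1 defines the full analysis set as everyone randomised. The ITT set "is a subset of the FAS that consists of all patients for whom the primary endpoint is available"; the section does not say when an endpoint counts as available. The PP set holds the same patients, classed by treatment received. Section 11.4.2 runs the primary Cox analysis on the PP set.

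**Missing data.** Section 11.5 states: "We will strive to make a complete case analysis". It expects this to be feasible because treating physicians can be asked about events, and it would consider multiple imputation if much is missing.

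**Withdrawal.** Sections 8.5 and 9.2.5 carry the same text and divide withdrawers by phase. For the treatment phase: "Patients who choose to withdraw from the study during the treatment intervention will be considered as drop-outs". Nothing is said there about asking for the outcome or about censoring. Patients who withdraw during follow-up are asked whether their physician may be approached for the primary outcome. If they refuse, "their data will be considered right-censored from the last documented contact onward".

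**Unreachable patients.** Section 9.2.1: "If a patient cannot be reached, the treating physician will be contacted to inquire about the possibility of the" patient's death. Section 10.1.3 has the physician asked for the primary outcome when a participant is lost without having asked to leave. It also seeks permission to obtain that outcome from leavers with a serious adverse event.

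**Replacement.** Section 7.4: "Substitute patients for drop-outs will be recruited". Section 11.5: "Patients who leave the trial during the blinded treatment phase are replaced only if the number of total drop-outs" exceeds 10%.

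**The concern.** Membership of both analysis sets turns on something observed after randomisation. Because ITT and PP contain the same people, comparing them cannot show what this selection does. A Cox model does not need complete follow-up: a patient who leaves early contributes time at risk until the last contact. The sample-size model in section 11.2 spreads drop-out evenly over all six months, so it expects some drop-outs in the treatment phase.

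Outcome collection is also weakest where it matters most. The arms receive different treatment only in the first four weeks (section 8.1), and this is the phase for which no inquiry on withdrawal is written. Under sections 7.4 and 8.3, unplanned glucocorticoid use can be started by the patient or the treating physician. It counts as a primary event, but it is not in itself a serious adverse event under section 10.1.1. A patient who stops feeling well, leaves, and restarts a glucocorticoid without being admitted can therefore go unrecorded. If this happened more often after abrupt stop, the comparison would lean towards non-inferiority.

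**Working it through.** **Inputs (section 11.2 unless stated).** Two-sided 95% CI, power 80%, 1:1 allocation, 40% events at 6 months in each arm, margin 13 points, 10% drop-out uniform over 6 months, N = 573. The treatment phase is 28 of 180 days (section 8.1 and the study schedule).

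**The plan's own figures.**
- Critical hazard ratio: ln(0.60 − 0.13) / ln(0.60) = ln(0.47) / ln(0.60) = 1.478, as stated.
- Events (Schoenfeld): 4 × (1.960 + 0.842)² / (ln 1.478)² = 206 after rounding up.
- Patients: 206 / 0.40 = 515; 515 / 0.90 = 573 after rounding up, as stated.

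The protocol reached 573 by simulation. This closed form matches it while giving drop-outs no information at all.

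**Power cost of excluding instead of censoring.**
- λ = −ln 0.60 = 0.511 per 6 months. The chance of an event before a uniform drop-out time is 1 − 0.40/0.511 = 0.217.
- With censoring, the event share is 0.9 × 0.40 + 0.1 × 0.217 = 0.382. At N = 573 power is 0.824 (0.823 simulated). For 80% power, 206 / 0.3817 = 540 patients would do.
- With all drop-outs excluded, the event share is 0.9 × 0.40 = 0.36, and power is 0.801 (0.806 simulated).
- Uniform drop-out gives 57.3 × 28/180 = 8.9, so about 9 of 57 drop-outs fall in the treatment phase. Excluding only these and censoring the rest leaves 0.823.

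**Type I error.** Data were simulated at a true hazard ratio of 1.478 with N = 573 under the exponential model of section 11.2 and analysed with an unstratified Cox model, 6,000 trials per cell. The Monte Carlo standard error near 0.025 is √(0.025 × 0.975 / 6000) = 0.002. Expected failures before day 28 in the abrupt-stop arm: 286.5 × (1 − exp(−0.511 × 1.478 × 28/180)) = about 32. The share of these lost is an assumption; the protocol gives no figure.

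| Share of early failures lost | Patients lost | Outcome retrieved | Censored | Excluded |
|---|---|---|---|---|
| 10%, abrupt-stop arm only | about 3 | 0.028 | 0.036 | 0.036 |
| 25%, abrupt-stop arm only | about 8 | 0.025 | 0.061 | 0.064 |
| 50%, abrupt-stop arm only | about 16 | 0.027 | 0.125 | 0.128 |
| 75%, abrupt-stop arm only | about 24 | 0.022 | 0.243 | 0.243 |
| 25%, both arms | about 13 in all | 0.025 | 0.027 | 0.025 |
| 50%, both arms | about 27 in all | 0.026 | 0.022 | 0.024 |

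With 25% or 50% lost in one arm and excluded, the average estimated hazard ratio falls from about 1.48 to 1.40 or 1.34. Censoring and exclusion behave almost alike; what protects the test is learning the outcome.

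**The case against.** A reader might infer that early drop-outs are never asked for their outcome, are certainly removed, are then replaced, and that the type I error is therefore inflated. The documents do not support that reading.

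- **Removal is inferred.** The availability condition is undefined. A censored time could satisfy it, and an event recorded before withdrawal certainly does. The complete-case sentence in 11.5 can be read as aiming for full outcome data, and multiple imputation is mentioned next. This stands as a limit on the claim, but not as an answer. Sections 8.5 and 9.2.5 set drop-out against being kept in the study, so exclusion is still the natural reading.
- **Retrieval exists for many patients.** Section 10.1.3 covers leavers with a serious adverse event, which includes hospitalisation and death, and patients lost without withdrawing. Section 9.2.2 has physicians asked about glucocorticoid dose. This narrows the gap to voluntary treatment-phase withdrawers without a serious adverse event.
- **No direct contradiction on censoring.** The censoring rule in 8.5 is written for follow-up withdrawers, and the one in 11.2 for patients still event-free at 6 months. The tension is between censoring as a principle and a set defined by availability.
- **Replacement is conditional in 11.5**, and recruiting further randomised patients does not itself create bias. What remains is the disagreement with 7.4.
- **One-armed loss is assumed.** The trial is planned as double-blind, patients hold rescue tablets whose use is itself an event, staying in the study does not bar open-label treatment, and outcomes are asked about from day 7. All of this makes large, unequal loss less likely. It does not exclude it, since patients may feel a difference that the blind does not hide.

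The analysis plan, which is not shown, could define availability. It could not recover outcomes that were never requested, and section 11.4.6 calls for an amendment if the analyses change substantially.

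**Conclusion.** The point holds in a limited form. The protocol makes membership of the primary analysis set depend on an undefined availability of the endpoint, and it writes no outcome inquiry for voluntary withdrawal in the four weeks when treatment differs, unless a serious adverse event has occurred. The patients chiefly affected are those whose event is unplanned glucocorticoid use. Two further pairs of rules conflict: 9.2.1 with 10.1.3 on what the physician of an unreachable patient is asked, and 7.4 with 11.5 on replacement.

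The power cost is small, about 2 points if every drop-out were excluded, and the stated 80% is still met. A bias is possible but not shown. It requires early failures to go unrecorded more often in the abrupt-stop arm. With about 8 or 16 such patients there and none in the control arm, the type I error would be about 0.06 or 0.13; with equal loss it stays nominal. Those shares are illustrations, not estimates. Redefining the set so that such patients are censored would not cure the bias by itself, so outcome collection is the more important half of the remedy.

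**What to change.** 1. **11.4.1:** define ITT as all randomised patients, analysed as randomised, without an availability condition.
2. **8.5 and 9.2.5:** ask treatment-phase withdrawers for the same permission as follow-up withdrawers, and censor at the last contact only when that inquiry fails.
3. **9.2.1:** align with 10.1.3, so that the physician of an unreachable patient is asked about every component of the primary outcome.
4. **11.5:** replace the complete-case sentence with a statement that censored patients stay in the model.
5. **7.4 and 11.5:** keep one replacement rule, and state that any further recruits are added and that no randomised patient is removed.

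The cost is amendment wording and a few extra questions in calls to physicians. The sample size need not change.

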### **8.4 Compliance with study intervention**

Patients will be asked to fill out a medication diary over the 4-week treatment phase. Adherence to study medication will be ascertained during the follow-up telephone visits at days 7 and 35 when patients will be asked to count tablets remaining in the vials ("pill count"). All patients will be asked to send back the spare tablets at the end of the treatment phase or return them at the visit on day 35, if this is a hospital visit. A sensitivity analysis will be performed to determine a compliance cutoff, i.e. a critical percentage of ingested study medication, below which an association with the outcome is visible.

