### 11.2 Determination of Sample Size

To assess the primary outcome measure, a Cox proportional hazards regression model will be fitted to the data. Non-inferiority will be concluded if the two-sided 95% confidence interval of the hazard ratio between the experimental and the control arm lies entirely below the critical hazard ratio defined as

$$HR = \frac{\lambda_e}{\lambda_c} = \frac{\frac{-\log(\pi_{et})}{t}}{\frac{-\log(\pi_{ct})}{t}} = \frac{\log(\pi_{et})}{\log(\pi_{ct})} = \frac{\log(\pi_{ct} - m)}{\log(\pi_{ct})}$$

where  $\lambda_e$  and  $\lambda_c$  are the hazard rates in the experimental and control arms,  $t$  is a fixed point of time,  $\pi_{et}$  and  $\pi_{ct}$  are the proportions of event-free patients at time  $t$ , and  $m$  is the non-inferiority margin expressed as the additional proportion of patients having had an event in the experimental arm, assuming that the occurrence of events follows an exponential distribution. Noninferiority will be concluded if the upper limit of the two-sided 95% confidence interval of the hazard ratio lies below the critical hazard ratio.

For the sample size estimation, the following assumptions were made:

- Patients are randomized to the control and experimental arms in a 1:1 ratio.
- After inclusion, all patients are followed for 6 months. Patients without an event within 6 months are considered right-censored and are not followed any further even though the trial might be ongoing.
- 10% of patients drop out within the 6 months follow-up period. The drop-out events are distributed uniformly over this period.
- The event rate within the 6 months follow-up period, i.e., the proportion of patients with an event, is 40%, both for the control and the experimental arms. We estimated this overall figure based on expected relapse rates for the various eligible diseases, as indicated by clinical experts and published data, e.g. in COPD or inflammatory bowel disease. Our estimation is conservative since the other components of the combined primary outcome will contribute to the event rate.
- The survival curves in the control and experimental arms follow the same exponential distribution. The rate parameter of the exponential distribution is chosen so that the corresponding cumulative distribution function value at 6 months equals the assumed event rate.

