#### 11.4.2 Primary Analysis

A Cox proportional hazards regression model with time to the (combined) primary endpoint as the response and treatment arm as the explanatory variable will be fitted, stratified after study centre, prednisone dose, and age group. Non-inferiority will be concluded if the two-sided 95% confidence interval of the hazard ratio (HR) between the experimental and the control arm lies entirely below the critical HR ratio of 1.478. The analysis will be conducted on the PP set.

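### The set called per protocol is an as-treated set with no rule for treatment obtained, and it is the only set named for the non-inferiority decision

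*Protocol*

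**What the plan says.** Protocol 11.4.1 defines three sets. The full analysis set is everyone randomised. The ITT set is the part of it with an available primary endpoint, analysed as randomised. The PP set "includes the same patients as the ITT set, but patients are assigned to the treatment arm that corresponds to the actually obtained treatment".

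Protocol 11.4.2 fits the Cox model, compares the confidence interval of the hazard ratio with 1.478, and fixes the set: "The analysis will be conducted on the PP set". Section 11.4 gives the ITT set no part in the primary analysis.

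Three other places bear on treatment obtained:
- **5.1 and 7.4.** Unplanned systemic glucocorticoid is part of the composite endpoint; 7.4 says that "unplanned (rescue) glucocorticoid treatment will be assessed as component of the primary outcome".
- **8.3 and 8.6.** The treating physician or the patient may start open-label glucocorticoid, also during the blinded weeks, and every participant is given emergency prednisone tablets.
- **7.4.** Non-compliance is listed among the reasons for excluding a patient.

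**The concern.** A per-protocol set normally removes major deviators and leaves everyone else in the randomised arm. The set in 11.4.1 does the reverse: it removes no one beyond those already missing from the ITT set, and it changes arm labels. Non-compliance as a reason for exclusion in 7.4 has no counterpart in the definition.

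The label is hard to assign in this trial because the arms differ by whether prednisone is taken, and taking unplanned glucocorticoid is itself an endpoint event. A placebo patient who starts open-label prednisone in week 2 has had an event and has also received prednisone. 11.4.1 does not say which arm this patient belongs to, or where a taper patient belongs who stops the tablets. If the label can depend on the outcome, the sole confirmatory comparison is no longer protected by randomisation.

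**Working it through.** **Inputs.** From 11.2: "the proportion of patients with an event, is 40%, both for the control and the experimental arms"; margin 13 percentage points over 6 months; 10% drop-out, spread uniformly; 1:1 allocation; 80% power; and the rule "Noninferiority will be concluded if the upper limit of the two-sided 95% confidence interval of the hazard ratio lies below the critical hazard ratio". Assumed, because the protocol gives no figure: the share of patients re-labelled. Simplification: the simulated Cox models are unstratified, whereas 11.4.2 stratifies by centre, dose and age group.

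**1. The plan's own figures.** They reproduce.
- Critical HR = ln(0.60 − 0.13) / ln(0.60) = 1.478.
- Events (Schoenfeld) = 4 × (1.960 + 0.842)² / (ln 1.478)² = 206 after rounding up.
- N = 206 / (0.40 × 0.90) = 572.2, so 573. The protocol, which used simulation, states: "To achieve a power of 80%, 573 patients (95% CI, 565 to 580) need to be included".

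The sample size is not at fault.

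**2. Patients whose label could be in doubt by day 28.** The true HR is set at 1.478.
- Control hazard per month = −ln(0.60) / 6 = 0.0851; abrupt-stop hazard = 0.0851 × 1.478 = 0.1258.
- Probability of an event by day 28 = 1 − exp(−0.1258 × 28/30.4) = 0.109.
- With 286 patients in the arm: 286 × 0.109 = about 31.

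**3. If a share of these 31 is counted in the taper arm.** Exponential event times, n = 573, 3,000-4,000 runs per row, same decision rule. A sound analysis would claim non-inferiority in about 2.5% of runs.

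| Share re-labelled | Patients (share × 31.3) | Mean HR | False non-inferiority |
|---|---|---|---|
| none (as randomised) | 0 | 1.48 | 2.8% |
| 5% | about 2 | 1.45 | 4.1% |
| 10% | about 3 | 1.42 | 6.0% |
| 25% | about 8 | 1.32 | 15% |
| 50% | about 16 | 1.18 | 44% |

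A separate set of 4,000 runs per scenario gave 2.2%, 16% and 47% for none, 25% and 50%. Differences of this size do not affect the conclusion.

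**4. Other meanings of treatment obtained, same true HR.**
- *Random crossover of 2-10%, such as a wrong vial, with the effect following the drug taken:* as-treated analysis gives 2.1-2.6%; as-randomised analysis gives 3.4-8.6%, because crossover dilutes the difference.
- *Switching related to prognosis.* Assumed: half the patients at double risk, high-risk placebo patients taking steroid, low-risk taper patients stopping tablets. With 5% switching, 5.0% as treated against 3.8% as randomised; with 10%, 8.9% against 5.8%; with 20%, 22% against 10%.

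So the harm from re-labelling depends on why patients change label.

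**5. Power if a true PP set must also succeed.** From 206 events, power = Φ(ln 1.478 × √events / 2 − 1.960).
- 5% excluded: 196 events, about 78%. Keeping 80% in that set needs 573 / 0.95 = 604 patients.
- 10% excluded: 185 events, about 76%. Keeping 80% needs 573 / 0.90 = 637 patients.

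The exclusion rates are assumptions.

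**The case against.** The strongest reply is that nothing in the protocol moves a rescued placebo patient into the taper arm. Sections 8.1 and 8.2 define the arms by the study vial and its four-week schedule, and someone taking emergency tablets has not received that schedule. Sections 7.4 and 8.6 treat rescue as an outcome and do not call it a change of arm. This stands. A reader might infer that the planned analysis is biased towards non-inferiority; the text does not support that. It leaves the reading open, and the figures in the table apply only if the reading is taken. If the rule merely corrects random dispensing errors, the as-treated analysis keeps its error rate and as-randomised analysis alone is the more lenient one.

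A second reply is that the statistical analysis plan may add an ITT run and a deviation list. It may, so one cannot say that no ITT analysis of the primary outcome will be done. But the protocol itself fixes the PP definition and the set for the primary test, and 11.4.6 requires an amendment for substantial changes to the analyses it outlines.

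A reader might also take the search in 8.4 for a compliance cutoff, described as "a critical percentage of ingested study medication, below which an association with the outcome is visible", to define the PP set. The protocol presents it as a sensitivity analysis and does not link it to the primary test, so it is no part of this point.

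**Conclusion.** The point holds as a defect of definition in the one analysis that decides the trial. The set is as-treated, has no exclusions for deviations despite 7.4, has no rule for treatment obtained, and is the only one named for the primary test. The possible cost ranges from nothing, if re-assignment follows random dispensing errors, to a false non-inferiority rate of about 15% if some 8 abrupt-stop patients with early events are re-labelled, and about 45% if some 16 are. These rates rest on a true HR of 1.478, exponential event times, an unstratified model and assumed shares. Even on the harmless reading the set is almost the ITT set, so the protocol has no per-protocol analysis to set beside it.

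**What to change.** - **11.4.2:** make the primary analysis all randomised patients in their randomised arm. Censor at last contact, as 8.5 and 9.2.5 already foresee for those who withdraw in follow-up and decline further inquiry, and say that the same applies to withdrawals during treatment.
- **11.4.1:** delete the re-assignment by treatment obtained. State that open-label or rescue glucocorticoid is an endpoint event and never changes the analysis arm.
- **11.4.1:** redefine PP as patients without major deviations, kept in their randomised arm. Fix the deviation list before unblinding, count adherence only up to the first event or day 28, and reconcile the definition with 7.4.
- Report PP as the companion analysis that should support the conclusion. This matters because as-randomised analysis alone is lenient when crossover dilutes the difference.

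**Cost:** a protocol amendment to these sections and one further model run, with no new data. The as-randomised analysis still needs 573 patients. If both sets must succeed, the protocol should state the lower power in the PP set, about 78% or 76% with 5% or 10% excluded.
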